## Abstract

**Background:**

Heart failure is a chronic disease affecting patient morbidity and mortality. Current guidelines for heart failure patient treatment are focused on improving their clinical status, functional capacity, and quality of life. However, these guidelines implement numerous instructions including medical treatment adherence, physical activity, and self-care management. The complexity of the therapeutic instructions makes them difficult to follow especially by older adults.

**Objective:**

The challenge of this project is to (1) measure real-life adherence to a regular physical exercise program and (2) attempt to influence older adult patients with heart failure toward embracing a more physically active self-care lifestyle.

**Methods:**

This research consists of two studies, including a lab experiment and a pragmatic evaluation of technology at patients’ homes. The lab experiment aims at exploring in an objective way (measuring neurophysiological responses to stimuli) patient engagement with different characteristics of virtual agents, while the home study is a 3-phase prospective study where the developed technology platform is tested by heart failure patients in their own home environments. Patients undergo evaluation of their physical activity and cognitive status using standard evaluation methods (6-minute walk test, questionnaires) and receive wearable devices to accurately measure everyday life activity levels (home study phases 1-3). During home study phases 2 and 3, exergames (serious games for physical exercise) to provide a physical exercise plan as a joyful activity are delivered to patients’ private households and e-coaching techniques are implemented in the final phase (home study phase 3) of the protocol, to influence patient attitudes toward a more healthy and recommended lifestyle.

**Results:**

The trial is still ongoing. Recruitment is ongoing, and the project has progressed for some participants through phase 2 of the home study. The sample size for both studies is 28 participants; 10 have already been included in the study, and both baseline clinical and patient-reported outcome data are retrieved. Phases 2 and 3 of the home pilot study are expected to be completed within 6 months.

**Conclusions:**

The main challenge of the project is the change of attitude of older age heart failure patients through an e-coaching system. Given the adoption of a cocreation and living lab approach and the main objective for real-life evaluation, the project is ready to react to any collected feedback, even during the implementation of the research plan. Clinical assessment and objective evaluation are expected to provide all required information for reliable findings.

**Trial Registration:**

ClinicalTrials.gov NCT03877328; https://clinicaltrials.gov/ct2/show/NCT03877328

**International Registered Report Identifier (IRRID):**

DERR1-10.2196/17714

## Introduction

### Background

Heart failure (HF) is a clinical syndrome affecting more than 15 million people in Europe and more than 30 million patients worldwide [1]. Despite advances in its management, prevalence of the disease is expected to increase mainly due to the aging of population, making the disease a constantly worsening global problem. Studies have proven the effectiveness of rehabilitation programs consisting of systematic physical exercise and self-care in HF patients [2-6]. Among them, regular aerobic exercise is recommended in HF patients in order to improve their functional capacity and symptoms [7]. However, changing lifestyle and engaging self-care, especially in older adults, is a difficult task and a barrier to engaging older adults with HF in regular physical exercise. Although therapeutic interventions seem to reduce admission rates for patients with HF, effective management of the disease remains a contemporary challenge. Current guidelines for HF patients emphasize improvement of clinical status, functional capacity, and quality of life, implementing complex regimens of multiple self-care behaviors (systematic exercise, fluid and sodium restriction, adherence to medical therapy, and close monitoring of the development of disease symptoms, etc) to medical treatment [7]. The complexity of the instructions and necessity of lifestyle modifications in combination with possible comorbidities and cognitive decline make the guidelines difficult to follow, especially in older adults [3].

The challenge of this project is to measure real-life adherence to a regular physical exercise program and attempt to influence older age patients with HF toward being more active. To do so, BioTechCOACH-ForALL uses wearable devices to measure activity levels, exergames (serious games for physical exercise) to deliver a physical exercise plan as a joyful activity, and e-coaching techniques to influence patient attitudes toward HF self-care and more healthy lifestyles.

### Protocol Concept and Rationale

Cardiovascular disease is common among older adults. In developed countries, prevalence of HF in adult population is 1% to 2%, rising up to more than 10% in people over 70 years old [1]. Late complications of the disease and comorbidities such as coronary artery disease, systemic arterial hypertension, diabetes mellitus, history of stroke, anemia, dementia, kidney dysfunction, lung disease, and obesity contribute to the burden of hospitalizations and mortality [7] and are targets of treatment.

According to current guidelines, the goals of treatment in patients with HF are to improve clinical status, functional capacity, and quality of life. Although these are surrogate markers of treatment success, the need for reduction of hospitalizations and mortality is also clearly indicated [7]. Furthermore, lifestyle modifications like implementing healthy nutrition and systematic exercise and smoking cessation as well as self-care including but not limited to monitoring body weight and avoiding excessive fluid and salt intake are deemed necessary [2]. Although the disease may sometimes be life-limiting, exercise is encouraged in all clinically stable patients with HF, and regular aerobic exercise is recommended in HF patients (class IA according to current guidelines [7]) in order to improve their functional capacity and symptoms [8]. Various exercise rehabilitation programs have been used in HF, consisting of bicycle ergometer training, dumbbell training using low weight (<1 kilogram), respiratory training, and walking about 5 times per week. Fatigue severity, 6-minute walking distance, respiratory function, and quality of life are improved via increased physical activity of HF patients [7,8]. To this extent, close monitoring of daily mobility and sedentary patterns with wearables and tailor-made e-coaching systems based on activity profiles and routines of HF patients, implemented in everyday life, may promote exercise integration by making it challenging for the patient, who may set their own realistic activity goals.

Patients with HF should also follow their medical pharmacotherapy, a task that might be difficult because of cognitive disorders and coexisting comorbidities leading to polypharmacy, often obligating a caregiver to help them with this daily task. Despite clear evidence of the benefits of adherence to medical therapy to the rates of morbidity and mortality and number of cardiovascular-related emergency department visits in HF, rates of patient adherence to medical and supportive therapy (the extent to which a patient’s behavior with regard to medication intake or lifestyle changes is consistent with therapeutic recommendations) vary significantly, fluctuating between 10% and 98% [7,9,10]. On the other hand, there is more clear evidence on the nonadherence (noncompliance to treatment) of patients, which was found to be almost 25% in the general population, with men and women showing the same rates of noncompliance to treatment. It has been shown that adherence to HF medication is related to patient institutionalization (including hospitalizations and nursing home visits) [11], while patient self-care (eg, self-care management; self-care maintenance; sodium, fluid, and alcohol intake restriction; physical activity; smoking cessation; monitoring signs and symptom; and keeping up follow-up appointments) is positively related to the length of time since the patient was diagnosed with the disease [12].

Given the constantly increasing number of patients with HF, patients’ demands on health care services are expected to increase greatly in the coming years. The need for more innovative and cost-effective treatment strategies led to studies of electronic health (eHealth) programs showing promising results in patients with HF [13-15]. These studies increased political and clinical attention to eHealth strategies as a mean of improving outcomes in patients with HF. However, the role of eHealth systems in the management of patients with HF and in particular in the practical implementation of adherence (eg, by promoting packages of measures concerning medical treatment and active living, patient education and active participation in the context of shared decision making to develop realistic expectations of their own disease course, and being active and adopting individual responsibility) is an emerging field of high scientific interest.

### Designing an eHealth System Using Virtual Coaches

Designing an eHealth system to promote self-care of patients remains challenging. User engagement constitutes a key component for considering technologies successful. O’Brien and Toms [16] defined user engagement as follows: “Engagement is a category of user experience characterized by attributes of challenge, positive affect, endurability, aesthetic and sensory appeal, attention, feedback, variety/novelty, interactivity, and perceived user control.” At the same time, the presence of human social models has been shown to affect attitudes, beliefs, and behaviors of users [17,18]. Moreover, anthropomorphic agents could have impact on cognitive functioning and exert social influence comparable to that of humans [16] while also promoting motivational characteristics such as self-efficacy and attitude change [19]. Furthermore, the use of pedagogical or virtual agents could facilitate learning [20]. Therefore, using a virtual coach with specific characteristics could possibly increase both technology acceptance and user engagement.

The influence of virtual agents on users could vary depending on different characteristics such as availability, communication skills, believability, functionality, and customizability in appearance [20]. In that sense, social models were found to be more effective as they resemble the observer or a projected ideal virtual self of the observer [19]. Existing evidence on learning showed that agents who had similar characteristics to trainees, with respect to appearance-related traits such as age and race/ethnicity, could be more influential [19]. However, prior expectations and stereotypes could influence the desired outcomes [20]. Additionally, perception of self in a virtual environment affects task-related, verbal, and nonverbal behaviors [21]. In line with that, researchers introduced the Proteus effect, which describes the condition where people conform to their avatar representation regardless of how other people perceive them [22]. Another study showed that a physically similar avatar to the observer could affect the emotional valence and arousal more than a neutral one. Additionally, the induced emotional states were more intense than those from neutral avatars [23]. Therefore, appearance is considered to be an important attribute while designing a virtual agent. Another important design element was shown to be that the agent stays within the field of vision of the participants [24,25].

The way that a virtual agent uses to communicate is another component for customization. Social presence consists of verbal and nonverbal cues. However, agent communication through voice has been found to be more beneficial than text. More precisely, the use of a human-like voice could enhance social presence and interaction with technology [16]. Moreover, facial expressions and deictic gestures are considered to be crucial for promoting learning-related outcomes. However, the large-scale study of Baylor and Kim [19] stressed that facial expressions—but not gestures—seem to enhance focus on the motivational message delivered by the virtual agent.

The evaluation of technology acceptance and user engagement in an explicit way remains a challenge. Fairclough et al [26] defined user engagement in a task in terms of cognitive activity (mental effort), motivation (approach or avoidance), and affective state (positive, negative), and they associated the user engagement’s components with psychophysiological measurements. Revisiting the literature, they found that increased theta activity in frontocentral sites along with decreased alpha activity in occipital sites was associated with higher mental effort due to working mental load. Pupil dilation was observed to be greater when complex cognitive processing is performed.

On the other hand, motivation and emotional experience (affect) were correlated to frontal asymmetry. More precisely, greater levels of left frontal activity were associated with positive emotions and motivational approach, whereas higher right frontal activity was linked to negative emotions and motivational avoidance. Other biomarkers of motivation were considered to be sympathetic nervous system indices, such as systolic blood pressure. In another study, user approval of an online avatar was explored by means of skin conductance, heart rate, and respiration. Results indicated that higher respirations were positively correlated with the degree of agent approval [27].

Peters et al [24] proposed user attention as another metric of human-agent interaction. They modeled user attention using three components: gaze detection; neurophysiological analysis; and an attention representation module for storage, integration, and interpretation of attention information.

### Study Objectives

High rates of noncompliance to treatment plan indicate the need for developing sustainable solutions to support and enhance the self-care of HF patients. BioTechCOACH-ForALL, implemented within the framework of the operational program Human Resource Development, Education, and Lifelong Learning and cofunded by the European Social Fund and national resources, investigates and researches a potential response to this challenge.

The main goals of the project are as follows:

Extension of previous experience in developing and applying innovative systems for physical training of elderly (webFitForAll [13]), in living labs or even at their home [28], encouraging physical exercise and promoting independent living. In addition, the e-coach platform will be enriched by a decision support system (smart algorithms that will personalize the interaction of the e-coach with patients) based on analysis and collection of interaction data. Commercial nonintrusive sensors will collect activity data in order to capture daily activity patterns [29] and activity volume. Daily activity patterns will be used to track their daily activity level regarding the doctor’s recommendation and readjust e-coaching system parameters (home study phases 1 and 2)Development of an e-coaching system (home study phase 3) based on neuroscience evidence (lab study), incorporating exergaming [30] and remote health monitoring [29] techniquesPatient engagement with different user interface interaction means, such as virtual projected coaches with different characteristics (presence/absence of medical uniform, gender, age) will be explored by means of electroencephalogram (EEG) and analyzing various biosignals such as heart rate, electrodermal activity, external body temperature, and eye gaze tracking

## Methods

### Overview

Two studies will be performed. The first study aims to optimize patient acceptance of the delivered technology solution and in particular the e-coaching virtual agent by evaluating different design characteristics introducing a novel lab experiment and objective measurement of patient engagement with the use of EEG and biosignal markers, while the second (at home) study aims to introduce the technologies and interventions (exergaming and e-coaching) to the HF patients’ daily routine. Results and findings of the first study will drive the design of the e-coaching intervention that will be applied in the third phase of the second study.

### Laboratory Study

The rationale of EEG study is to explicitly capture the way patients perceive images of virtual agents by recording different biosignals. In that sense, analysis of multichannel event-related EEG data could reveal differences in spatial distribution and temporal sequencing of neural activity between different conditions such as presence versus absence of medical uniform, old versus young, and female versus male [21,31,32]. Moreover, other biosignals such as electrodermal activity, external body temperature, heart rate, and eye gaze tracking have already been applied to evaluate affective and cognitive impact of projected stimuli [24,33]. As such, HF patients will undergo a 2-part experimental procedure in which various biosignals will be recorded via EEG, E4 smartwatch (Empatica Inc), and GP3 eye tracker device (Gazepoint). In both parts of the experimental procedure, participants were instructed to freely observe the images. In the first part, participants will passively observe images of virtual agents, presented on screen as stimuli having different appearance characteristics such as age, gender, and presence/absence of medical uniform. In the second part, stimuli presented to participants will be pairs of virtual agents followed by a fixation cross on black background. The pair of agents differs regarding the presence/absence of medical uniform but preserves all other characteristics (age, gender).

### At-Home Study Design

#### General Design

BioTechCOACH-ForALL home study is a prospective, multiple baseline across subjects, nonrandomized, single-arm, single-center study following a within-subject design to assess the feasibility and efficacy of the Virtual Coach Program in older age patients with HF. The study will be delivered in three phases, each of them fulfilling a different scope. All participants will go through all study phases. Each phase will allow participants to familiarize themselves with the delivered technology of that phase. A multiple baseline approach will be followed so that the effects of each phase are as isolated to the previous phases as possible, allowing for effect comparison among them. Clinical and quality of life assessment and exercise behavior and attitude will be measured repeatedly in both the baseline phase and the two intervention phases. This way any cause-effect relationships among the intervention and patient outcome measures will be demonstrated.

The study conforms to the ethical guidelines of the 1975 Declaration of Helsinki, all participants will sign informed consent, and the study protocol has been approved by the bioethics committee of the School of Medicine of the Aristotle University of Thessaloniki (Protocol No. 1.45/21.11.2018) and registered at ClinicalTrials.gov [NCT03877328]. The study protocol is structured in a manner that incorporates three different phases, coming one after the other. Each patient will enter the study in the phase 1 and complete their participation in phase 3.

#### Phase 1

Phase 1 introduces the objective measurement technology, the wearable monitoring device. This technology will be running throughout the project’s lifetime and will provide objective information on patient activity. This information, along with the doctor’s baseline and intermediate assessment, will be used as an indicator of the effectiveness of phases 2 and 3.

#### Phase 2

Phase 2 introduces a joyful way of exercising, allowing patients to exercise in the comfort of their homes. Patients will be assigned a structured recommended schedule with a goal of 3 sessions per week for a total of 36 sessions in 3 months. Frequency and intensity of the training program are indicated by patient functional capacity. All patients will undergo a 6-minute walk test, and their performance will be used for determination of the exercise program. By protocol, patients performing more than 500 meters in the 6-minute walk test at baseline will be prescribed a more intense exercise program in terms of the number of exercise repetitions. The exercise protocol offers 50 minutes of exercise implementing aerobic and resistance endurance exercises including upper and lower extremities. Regular blood pressure and heart rate monitoring will be performed manually by the patient with the use of dedicated devices in time intervals specified in the protocol. Exercises will be implemented as fun, full-body interactions, processed and recognized through a depth-camera–based sensor and computer vision and translated into computer game actions and scenarios integrated within a Web application [14].

#### Phase 3

Phase 3 introduces the coaching aspects, where exergames are introduced and delivered through home surface projection, apart from the personalized recommendations and suggestions (designed by the doctor).

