### Clinical Assessment

Patients will be clinically evaluated before entering each of the two studies and on the initiation of each protocol phase (meaning before entering phase 1, phase 2, and phase 3, and at the end of phase 3, which will mark the end of study), completing 4 on-site clinical visits for the impact of each intervention to be assessed.

On the baseline, intermediate, and follow-up assessments, patient clinical condition, quality of life, and health-related costs will be considered. More specifically, blood pressure, heart rate, blood oxygen saturation, and body weight will be measured for the clinical assessment. To assess physical status, the 6-minute walk test and NYHA functional class will be used for exercise intolerance. Patient-related outcomes to be used include the Beck Depression Inventory [42] and the Dukes questionnaire [43]. As for the evaluation of quality of life, the Short Form Health Survey questionnaire [44,45] will be employed. Self-efficacy for exercise behavior scale will be used for evaluation of changes in patient perspectives on exercise [46]. Finally, for health-related costs, the effect on number of hospital admissions along with the effect on health care use (number of primary and secondary care contacts, social care contacts, relevant medication use) will be calculated during all three phases.

Real-world data will be collected continuously (across all phases of the home study) to assess several aspects of the interventions planned. Continuously measured activity levels expressed in daily steps taken by the patient will be compared across the different study phases. Real-life adherence of the HF patients to the proposed intervention will be measured in terms of attendance at the webFitForAll platform using wearable heart rate monitoring data as well as online activity logs and telephone and clinic follow-up. Real-world adherence will be compared within-subjects for the second and third phases of the study. Use analytics (virtual coach used, content and delivery time of messages/recommendations) of the e-coaching system and juxtaposed relevant outcomes (such as activity levels collected by the activity tracker and adherence to the webFitForAll training program given any system logs) will be routinely collected. Patients adherence will be evaluated by measuring attendance at the webFitForAll and heart rate monitoring data as well as by activity logs and telephone and clinic follow-up.

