### Statistical Analysis

Continuous variables with normal distribution will be reported as mean and standard deviation, while those with nonnormal distribution as median and interquartile range. Categorical variables will be expressed as frequencies and percentages. Continuously data collected will be explored for normality assumption by means of a Shapiro-Wilk test to calculate the appropriate descriptive statistics [47].

Repeated measured analysis of variance or Friedman test will be used to assess changes on continuous data with normal and nonnormal distribution, respectively, between baseline, follow-up, and end-of-study visits. Possible associations between variables will be investigated using Pearson or Spearman correlation coefficients. We estimated sample size conducting power analysis using G*Power software (version 3.1). We performed repeated measures analysis of variance (3 time conditions) using 80% power, a medium effect size of 0.25, and significance level of 5%. The sample size was estimated to be 28 participants. One-third of this patient population that will agree to proceed to home study (phases 1 through 3) will enter the next steps of study protocol [48]. All statistical analyses will be performed using SPSS Statistics version 23.0 (IBM Corp) or R for Windows version 3.1.3 (R Foundation for Statistical Computing).

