### Strengths and Limitations

An important strength of this study is the fact that is the first to examine the potential of neuroscience-backed e-coaching toward patient activation and adoption of active lifestyle by HF patients. There is currently a significant gap with respect to the adoption and use adherence by chronic patients of eHealth interventions delivered at home.

This study also has some limitations. As heart failure with reduced ejection fraction is more common in men than in women (who in turn are more susceptible to heart failure with preserved ejection fraction), the percentage of male participants is expected to outrange that of females. So far, only male participants have accepted and started the study. In addition, as the inclusion criteria indicate, only patients with adequate level of technology proficiency can participate in the study. This fact complicates the generalizability of the results for older HF patients and women in particular.

The second limitation is that the nature of this study (single-case series) does not allow for a distinct control group. Each case will serve as both control and intervention participant, and analysis will be performed on an individual basis. However, one of the main strengths of this evaluation design is its real-life nature and that any validity threats will be mitigated by detailing the context and participants when results are reported.

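### The article promises repeated measurement in every phase and patient-level, cause-effect analysis, but the visit outcomes are taken only at four phase boundaries and have only group-level tests

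*Protocol article*

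**What the plan says.** General Design labels the home study a "multiple baseline across subjects, nonrandomized, single-arm, single-center study following a within-subject design". It says that clinical and quality-of-life assessment and "exercise behavior and attitude will be measured repeatedly in both the baseline phase and the two intervention phases", and then: "This way any cause-effect relationships among the intervention and patient outcome measures will be demonstrated".

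Strengths and Limitations calls the study a single-case series without a separate control group: "Each case will serve as both control and intervention participant, and analysis will be performed on an individual basis".

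Clinical Assessment fixes the visits: "before entering phase 1, phase 2, and phase 3, and at the end of phase 3, which will mark the end of study", with patients "completing 4 on-site clinical visits for the impact of each intervention to be assessed". It assigns the 6-minute walk test, NYHA class, Beck Depression Inventory, Dukes questionnaire, Short Form survey and exercise self-efficacy scale to these baseline, intermediate and follow-up assessments. Daily steps are recorded continuously across all phases. Attendance on the exercise platform is compared between phases 2 and 3.

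Statistical Analysis says: "Repeated measured analysis of variance or Friedman test will be used to assess changes on continuous data". Apart from descriptive summaries and correlations, it gives no other method for the visit outcomes.

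**The concern.** When a patient is his own control and is analysed individually, the evidence comes from several values inside each phase. They show how much that patient varies when nothing has changed, and a shift at a phase change is judged against that variation. General Design says this property holds for all the listed outcomes and rests its causal claim on it. For the visit outcomes, the stated schedule does not supply it.

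The abstract and the Discussion both name change of attitude as the project's main challenge. The instrument given for patients' views on exercise is the self-efficacy scale, one of the measures taken only at the boundaries. If the causal and individual wording stays, ordinary test-retest variation in one patient's scores could be reported as an effect of exergames or coaching.

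**Working it through.** **1. Which outcomes have a series inside each phase**

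| Outcome | Inside phase 1 | Inside phase 2 | Inside phase 3 | Section |
|---|---|---|---|---|
| Daily steps, heart rate, oxygen saturation (wearable) | yes | yes | yes | Wearable Monitoring; Phase 1; Clinical Assessment |
| Session attendance | not applicable | yes | yes | Clinical Assessment |
| 6-minute walk, NYHA, Beck, Dukes, Short Form, exercise self-efficacy | none stated | none stated | none stated | Clinical Assessment |

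The last row has values only at the four boundaries.

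**2. The plan's own figure.** Inputs from Statistical Analysis: repeated measures ANOVA, m = 3 time conditions, f = 0.25, 80% power, 5% level. Assumed, because not stated: correlation rho = 0.5 and no sphericity correction.

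- lambda = N·m·f²/(1 − rho) = 28 × 3 × 0.0625 / 0.5 = 10.5, with 2 and 54 degrees of freedom.
- Power = 0.812, and 28 is the smallest N reaching 80%. The stated 28 is reproduced.

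This is a test of group means. It gives no support for an analysis of single patients.

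**3. One patient's own visits, by exchange test.** Two visits (before phases 1 and 2) precede any exercise or coaching. Two (before phase 3 and at its end) follow. The smallest one-sided p is one over the number of ways to divide the visits:

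- 2 v 2: 1/C(4,2) = 1/6 = 0.17
- 2 v 1: 1/C(3,1) = 1/3 = 0.33
- 1 v 1: 1/C(2,1) = 1/2 = 0.50

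None reaches 5%, whatever the outcome or its reliability. Clinical Assessment also mentions an evaluation before each of the two studies. If the lab evaluation added a separate third pre-exercise value, 3 v 2 would give 1/C(5,2) = 0.10, still above 5%.

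**4. Size of a change that could be flagged, 6-minute walk.** The SD is 99.78 m and the mean 443.00 m (Results, 10 patients). Reliability (ICC) is not in the document and is an assumption, shown as a range. SEM = SD·√(1 − ICC).

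- Limit A, outside reliability figure, one value against one: 1.96·√2·SEM.
- Limit B, error pooled over the two phase 1 visits of about 9 home patients (28/3 = 9.3), a later value against the mean of those two: t(9 df) = 2.26, so 2.26·√1.5·SEM.
- Limit C, error from that patient's two phase 1 visits only: t(1 df) = 12.71, so 12.71·√1.5·SEM.

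| Assumed ICC | SEM (m) | A (m) | B (m) | C (m) |
|---|---|---|---|---|
| 0.80 | 44.6 | 123.7 | 123.6 | 694 |
| 0.90 | 31.6 | 87.5 | 87.4 | 491 |
| 0.98 | 14.1 | 39.1 | 39.1 | 220 |

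C is roughly half the mean walk or more throughout, so the patient's own visits are of no practical use for this. A and B are usable, but only for large changes, and both depend on the assumed reliability.

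**The case against.** A reader might infer that no individual change in a visit outcome can be told from measurement error. The documents do not support that. Two visits bracket phase 1 before any exercise or coaching, so error pooled over patients gives a threshold (limit B), and a large change could exceed it. That pooled error would also include learning and any effect of wearing the device.

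A reader might also infer that the effect the plan is sized for lies inside one patient's noise. Putting f = 0.25 on the walk test gives an SD of means of 0.25 × 99.78 = 24.9 m and, for three equally spaced means, a span of 2 × 24.9 × √1.5 = 61.1 m. At reliability 0.95 limit A is 61.8 m, and the order reverses just above that. The power calculation also names no endpoint. The inference therefore does not hold over the assumed range.

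Three further points stand in part:

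- Exercise behavior, heart rate and oxygen saturation are recorded within every phase, and the Phase 2 section adds patient-taken blood pressure and heart rate. The promise is kept for part of what General Design lists.
- Statistical Analysis already treats visit outcomes at group level, and nowhere is a patient to be declared improved on a pair of visits. That harm is a risk of the wording, not a stated plan.
- The sentence on individual analysis names no outcome and could be read as meaning the continuous series. General Design cannot be read so narrowly, since it names quality of life and attitude and draws the causal claim from their repeated measurement.

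Nor can the gap be put down to an article condensing a fuller protocol. The article states a visit schedule, and that schedule does not deliver the design it describes.

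**Conclusion.** The point holds for the 6-minute walk, NYHA class, Beck, Dukes, Short Form and exercise self-efficacy. The article attributes to them a property, repeated measurement within each phase supporting individual and causal conclusions, that its own schedule and tests do not provide. The exchange-test result (0.17 at best over the four visits) follows from the visit count alone and needs no assumption about reliability. The walk-test thresholds of about 124, 87 and 39 m rest on assumed reliabilities of 0.80, 0.90 and 0.98 and on an SD from 10 patients. They show that only large individual changes could be flagged, even with pooled or outside error.

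The point does not touch the group-level tests of visit outcomes. For the series recorded within phases it says only that they have the repeated values such an analysis needs; whether they suffice for a causal conclusion is a separate question.

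**What to change.** In General Design and in Strengths and Limitations, limit the individual-level, multiple-baseline and cause-effect statements to the series recorded within phases: daily steps and the other wearable measures across all three phases, and logged session attendance for phase 2 against phase 3 only. State that visit outcomes, including exercise self-efficacy, are reported as group changes by the tests in Statistical Analysis, without individual or causal claims. This costs a few sentences and no new data. Phases 2 and 3 were still to be completed when the article was written, so the change could be made before those results are reported.

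If an individual analysis of attitude is wanted, the self-efficacy scale would have to be repeated inside each phase. Three values per phase bring the smallest one-sided exchange p for phase against phase to 1/C(6,3) = 0.05, and five bring it to 1/C(10,5) = 0.004. This is optional and not shown to be cheap. Telephone follow-up is mentioned only for adherence, no call frequency is given and no phase 1 calls are described. It would also add questionnaire burden and familiarity with the scale.
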